#### The grief intensity scale

The GIS is a scale proposed by Prigerson et al. (30) and consists of 12 questions measuring the thoughts, emotions, and behaviors of individuals who have recently lost an important person. This scale represents the severity of the reactions of the bereaving individual. It facilitates clinicians to be able to assess the risk of an individual being later diagnosed with prolonged grief disorder after the loss of a loved one. The first two questions of this scale question the time elapsed since the death of a loved one and the decline in performance. The sum of the scores of the next 10 Likert-scale questions, each of which is answered with never, at least once a month, once a week, once a day, and several times a day, is analyzed as a grief intensity score. Each item receives a score of 1–5. A higher score represents a higher intensity of grief symptoms (31). We conducted a pilot study to investigate the validity and reliability of the Persian version of GIS and estimate the mean and standard deviation of the grief intensity score of the bereaved persons due to COVID-19. The face and content validity of the questionnaire was confirmed by the expert panel. Cronbach’s α of 0.92 and the intraclass correlation coefficient of 0.87 indicated good internal consistency and test–retest reliability of the Persian version of GIS.

#### The general health questionnaire

The GHQ-28 is designed for screening non-psychotic mental disorders and is commonly used among researchers all over the world. It consists of four subscales, such as somatic symptoms, anxiety symptoms, social functioning, and depressive symptoms. The Farsi version of the GHQ-28 has been validated by Noorbala et al. (32) for use in Iranians above 15 years old, and it has demonstrated good reliability and validity for research. The 28-item questionnaire includes multiple-choice questions accompanied by the following four possible responses: Not at all, No more than usual, Rather more than usual, and Much more than usual. A score ranging from 0 to 3 can be given for each response, with a total possible score ranging from 0 to 84. A higher total score is an indicator of poor general health, and 23 is the most reliable cut-off point for the presence of distress (32).

#### The short form health survey

The SF-12 is a short form of the SF-36 Health Survey with 12 questions and two main domains that provide glimpses into mental and physical functioning, including physical functioning (two items), bodily pain (two items), limitations in usual role activities because of physical problems (one item), general health (one item), vitality and energy (one item), social functioning (one item), limitations in usual role activities because of emotional problems (two items), and perceived mental health (two items). The individual’s score is calculated separately for the mental and physical component summary. The SF-12 has been validated for use in the Iranian population by Montazeri et al. (33), demonstrating Cronbach’s α of 0.72 and good reliability and validity.

#### The client satisfaction questionnaire

The CSQ-8 is a questionnaire proposed by Larsen et al., which is used to measure clients’ satisfaction rate with health services (34). This questionnaire consists of eight items, each question is accompanied by four responses from very positive to very negative, and each item gets a score of 1–4. The minimum total score is 8, and the maximum total score is 32. A higher score shows higher satisfaction with the services. The internal consistency of the questionnaire has been validated with Cronbach’s α of 0.91 (35). In the study of Imanzadeh et al. (36), the validity and reliability of the Persian version of CSQ-8 were approved.

#### Reducing loss to follow-up

For decreasing loss to follow-up of the participants, their phone numbers will be obtained at the beginning of the counseling sessions, and before each assessment, they will be reminded by phone 1 week before. If the participant does not attend, two follow-up telephone calls will be made. Calls will be at different times on different days, so the possibility of reaching the participant will increase. If, after two telephone calls, the participant is not willing to cooperate, the rater will try to fill out the GIS by phone and end the assessment.

### Blinding

It is obvious that we will not be able to blind the participants of the two groups toward the number of sessions, but the raters will not be among those clinical psychologists providing the grief counseling sessions and will be blind toward the number of sessions each individual has received. Those who are involved in the analysis of the data will also be blinded toward the participants’ affiliation to each group, as these data will be coded.

### Quality assurance

Before the study, the service providers will be trained in a 2-day workshop to be able to offer the trial service package. Raters will also be trained to fill out the questionnaires. One team will train the whole team of raters and service providers, and one single training module will be used. Quality assurance at the national level will be the responsibility of the “National Executive Committee.” One supervisor will be chosen from each university which will ensure keeping up with the study protocols and standards, including calls, counseling sessions, and ratings. One national coordinator will also be allocated for every two universities for further supervision.

### Sample size calculation

The sample size has been calculated to be 60 individuals in each group, which is a total of 120 individuals. Twelve individuals will be selected from two health centers of each of the 10 universities. This calculation has been done using the G*Power software (37) for comparing the grief intensity score as the primary outcome among the two groups and based on the results of the pilot study. In this calculation, the type one error (α) is 0.05, the type two error (β) is 0.2, the effect size (d) is 0.5, and the drop-out expectation is 20% of the participants.

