### Randomization

After informed consent, participants are randomized into three- or five-session intervention groups. Allocation of participants to each group will be done with the use of Stratified Balanced Block Randomization. Twelve participants will be selected from each university, and randomization will be done separately for each. Among 20 possibilities for six blocks including forms of three individuals in the five-session group and three individuals in the three-session group, two blocks will be randomly chosen for each university in the Microsoft Office Excel software with the use of the RANDBETWEEN formula and a random sequence will be formed. Subsequently, participants will be divided into the three- and five-session groups equally according to the random sequence. Randomization will be done in the main research headquarters in the Mental Health Research Center of the IUMS, and information will be only given to the health centers at the time of initiation of the intervention.

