### Planned analysis

The data, after entering and cleaning, will be analyzed using the SPSS V.18 and Stata V.11 software. Mean and standard deviation will be calculated to continuous data and frequency, and percent will be used for showing categorical variables. The analysis approach will be “intention to treat.” An independent and paired *t*-test, a chi-square, and a repeated-measures ANOVA (non-parametric tests if necessary) will be used to compare the studied outcomes in the follow-ups between and within the groups. The generalized estimating equations (GEEs) will be fitted in separate models for each outcome, and α < 0.05 will be considered as statistical significance.

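### The sample size section does not say whether alpha is one- or two-sided; under a conventional two-sided t-test, 60 per arm less 20% drop-out gives about 68% power at d = 0.5, not 80%

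*Protocol article*

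**What the plan says.** The Sample size calculation section of the protocol article gives the result, "The sample size has been calculated to be 60 individuals in each group, which is a total of 120 individuals", and the inputs: "the type one error (α) is 0.05" and "the type two error (β) is 0.2, the effect size (d) is 0.5, and the drop-out expectation is 20% of the participants". It says that G*Power was used to compare the grief intensity score between the two groups, drawing on a pilot study. It names neither the G*Power test nor the number of sides, and it does not say how drop-out was allowed for.

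Three other places bear on how to read these inputs:

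- The Introduction closes with a hypothesis of comparable or equal efficacy. It gives no direction and no margin.
- Data collection/management process defines the primary outcome as the grief intensity score at the 3-month follow-up.
- Planned analysis lists t-tests, chi-square, repeated-measures ANOVA and GEE models under one threshold, "α < 0.05 will be considered as statistical significance", again without a direction.

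Allocation is equal: "participants will be divided into the three- and five-session groups equally according to the random sequence".

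**The concern.** A standardised effect d, a comparison of two groups and a single primary time point together describe the ordinary two-sample t-test. For that test at two-sided 0.05, d = 0.5 and 80% power lead to the familiar 64 per arm before any loss. The plan enrols fewer than that and still expects to lose a fifth of them, so the stated figure cannot be right on this reading.

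The Introduction and Discussion say that, if the two courses look similar, the shorter one may be offered nationally. A non-significant difference is therefore a result that could be acted on, and readers will judge it by the stated power. If that power is nearer 68% than 80%, a null result is less informative than the article suggests. Whether similarity should be judged against a margin is a separate question and adds no weight here.

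**Working it through.** **Inputs** (Sample size calculation, with allocation from Randomization): alpha 0.05; power 1 − 0.2 = 0.80; d = 0.5, so a difference of 0.5 with SD 1; 1:1 allocation; 60 per arm; drop-out 20%, so 60 × 0.8 = 48 completers per arm (96 in total). Sidedness is not given, so both cases are run.

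**Step 1. Try to reproduce 60 per arm with the two-sample comparison.** By the normal approximation, n per arm = 2(z_alpha + z_power)² / d².

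- Two-sided: 2 × (1.960 + 0.842)² / 0.25 = 62.8, so 63; the noncentral t gives 64.
- One-sided: 2 × (1.645 + 0.842)² / 0.25 = 49.5, so 50; the noncentral t gives 51.

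Drop-out is then allowed for in two ways. Dividing by 0.8 delivers the required number of completers. Multiplying by 1.2 is a common shortcut that falls short of it.

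| Test | Evaluable per arm (normal / t) | ÷ 0.8 | × 1.2 |
|---|---|---|---|
| Two-sided 0.05 | 63 / 64 | 79 / 80 | 76 / 77 |
| One-sided 0.05 | 50 / 51 | 63 / 64 | 60 / 62 |

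No two-sided version of the unadjusted comparison gives 60. One combination does: one-sided, normal approximation, multiplied by 1.2. That is a numerical match, not evidence of what was done.

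**Step 2. Power of the stated design.** The noncentrality parameter is d√(n/2), with 2n − 2 degrees of freedom.

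- 48 per arm: 0.5 × √24 = 2.449. Two-sided power is 67.9% (normal approximation 68.8%); one-sided power is 78.4% (79.0%).
- 60 per arm, no drop-out: 0.5 × √30 = 2.739. Two-sided power is 77.5% (78.2%).

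If the test is two-sided, the type II error at 48 per arm is 1 − 0.679 = 32%, against the stated 20%.

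**Step 3. Detectable difference.** With 48 per arm and a two-sided t-test, 80% power is reached at d = 0.578, about 0.58.

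**Step 4. Analyses that use more than one measurement** (two-sided 0.05, 48 per arm). The article gives no correlation r between measurements, so r is an assumption throughout.

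- Baseline-adjusted comparison, residual SD √(1 − r²): noncentral-t power is 75%, 80% and 86% at r = 0.4, 0.5 and 0.6. At r = 0.5, for example, the noncentrality is 2.449 / √0.75 = 2.828.
- Mean of two follow-ups, SD √((1 + r)/2): 85% at r = 0.3, 79.9% at r = 0.5 and 75% at r = 0.7.
- Mean of three measurements, SD √((1 + 2r)/3): 80.8% at r = 0.6. This takes d = 0.5 to apply at every measurement, including baseline, where no effect is expected.

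**The case against.** The strongest reply is that the article never says two-sided, so the shortfall follows from an assumption that the reviewer supplies. That stands, and the 68% and 32% must carry the condition. A one-sided test is also not foreign to the aim: the question is whether the shorter course can replace the longer one, and only inferiority of three sessions would defeat that. On a one-sided 0.05 test the plan misses its stated power by just 1.6 points (78.4% against 80%). Against this, the article gives no direction and no margin, and ordinary difference tests are planned.

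The second reply is that Planned analysis includes repeated-measures ANOVA and GEE, and Step 4 shows that such analyses can reach about 80% with 96 completers on two sides. A reader might infer from Step 1 that only a one-sided test leads to 60; that is not so. These routes need a correlation that the article does not state, however, and the primary outcome is set at one time point, which favours the simple comparison.

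A reader might also infer that the sponsor found 50 per arm and wrongly multiplied by 1.2. The documents do not support this. No inflation rule is stated. The match needs the normal approximation, whereas the t-test figure of 51 gives 61.2. Twelve participants in each of ten universities also makes 120, so the total could have been set by that structure.

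**Conclusion.** The point holds as a conditional one. As written, the inputs in Sample size calculation do not lead to 60 per arm under the conventional two-sided, unadjusted t-test. That test needs 64 evaluable or 80 enrolled per arm (160 in total), and the planned 60 gives 67.9% power after drop-out and 77.5% without it. This rests on two assumptions: a two-sided alpha, and an analysis of the 3-month score without adjustment. Both fit the article best, but it states neither.

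The claim that the trial's true type II error is 32% whatever the analysis goes too far. Undeclared alternatives bring power close to 80%, and the derivation of 60 cannot be recovered from the document. What can be said is that the stated power is missed on the ordinary reading, narrowly missed on the one-sided reading, and reached otherwise only with a correlation that is not given.

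**What to change.** Keep 120 participants. In Sample size calculation, state the number of sides and the test behind the calculation, and restate the power. For a two-sided unadjusted comparison the text could read:

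*Sixty per arm, leaving 48 evaluable after 20% drop-out, gives 68% power at d = 0.5 (two-sided alpha 0.05, unadjusted t-test), or 80% power at d = 0.58.*

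If the primary analysis is baseline-adjusted, quote its power together with the assumed correlation (75%, 80% or 86% at r = 0.4, 0.5 or 0.6) and the source of that correlation; the pilot study would be the natural place to look. If a one-sided test was intended, say so, justify it, and give 78.4% at 48 per arm.

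The cost is one rewritten paragraph and, on the two-sided unadjusted reading, a less favourable power figure. No extra enrolment is needed.

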### Planned analysis

The data, after entering and cleaning, will be analyzed using the SPSS V.18 and Stata V.11 software. Mean and standard deviation will be calculated to continuous data and frequency, and percent will be used for showing categorical variables. The analysis approach will be “intention to treat.” An independent and paired *t*-test, a chi-square, and a repeated-measures ANOVA (non-parametric tests if necessary) will be used to compare the studied outcomes in the follow-ups between and within the groups. The generalized estimating equations (GEEs) will be fitted in separate models for each outcome, and α < 0.05 will be considered as statistical significance.

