### Recruitment process

Five of the researchers will be in direct connection with the 10 medical universities. In every university, two health centers will be selected for service delivery, and one trained clinical psychologist will be the service provider in each center. The clinical psychologist obtains names and phone numbers of bereaved people on a routine basis from the social service department of the hospitals in the catchment area of the center and will invite them by phone to encourage them to attend the grief counseling sessions. The clinical psychologist will also try to create effective communication and express compassion and empathy toward the grieving individuals. When participants attend health centers, their demographic data are obtained and registered, and the inclusion or exclusion criteria will then be re-assessed. If inclusion criteria exist and in the absence of the exclusion criteria, the participant will be thoroughly informed on the designed counseling intervention process, and informed consent will be obtained. If several family members of one COVID-19 victim attend the health center to receive service, only one of them will be enrolled in the study, and the rest will be directed to receive the usual grief counseling services provided at health centers. Assessments will be done at three time points, one before the intervention and the others 1 month and 3 months after the intervention.

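### The two-sample t-test named for between-group comparison uses neither baseline GIS nor university; an adjusted primary model would be more precise at almost no cost

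*Protocol article*

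**What the plan says.** Three parts of the protocol article bear on this point.

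- **Design.** The Randomization section makes university the stratum: "Twelve participants will be selected from each university, and randomization will be done separately for each". That gives 10 strata of 12, each filled from two blocks of six.
- **Measurement.** The Recruitment process section says: "Assessments will be done at three time points, one before the intervention and the others 1 month and 3 months after the intervention". The Data collection/management section makes GIS at the 3-month follow-up the primary outcome, so every participant should have a baseline value of that outcome.
- **Analysis.** For comparisons between and within arms, the Planned analysis section lists two-sample and paired t-tests, chi-square tests and repeated-measures ANOVA, with non-parametric tests where needed. It then says: "The generalized estimating equations (GEEs) will be fitted in separate models for each outcome". It names no covariate and does not say which method decides the primary comparison.

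The Sample size calculation section describes a two-group comparison of GIS and mentions no covariate or baseline correlation. It states: "The sample size has been calculated to be 60 individuals in each group, which is a total of 120 individuals".

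**The concern.** A two-sample t-test on 3-month GIS has no place for baseline GIS or university, and neither does its usual rank-based substitute. Two sources of explainable variance therefore stay in the error term.

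- **Baseline GIS.** People who start with more intense grief are likely to score higher later. If so, part of the 3-month variance is predictable from a measurement the trial already has.
- **University.** Blocking balances the arms within each university, so differences between universities largely cancel out of the treatment contrast. A test that ignores university still counts those differences as noise, and its standard error is somewhat too large.

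Precision matters here because of how the result will be used. The Introduction and Discussion say that if the two arms look similar, the three-session version can be offered to the authorities as a population-level service. Any judgement of similarity rests on the width of the interval for the difference, and a needlessly wide standard error makes a finding of no difference more likely.

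**Working it through.** **Inputs from the Sample size calculation section.** "the type one error (α) is 0.05, the type two error (β) is 0.2, the effect size (d) is 0.5". The same section allows for a loss of 20%. Completers: 60 × 0.8 = 48 per arm.

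**Inputs the article does not give (assumptions).**
- Correlation r between baseline and 3-month GIS: range 0.2 to 0.7. The 0.87 reported for the Persian GIS is test–retest reliability. It is not the correlation across a counselling course plus three months.
- Share of GIS variance between universities (ICC): range 0.01 to 0.10.
- Sidedness: two-sided as base case, one-sided also shown.

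**Step 1: the plan's own figure.** n per arm = 2(z_α + z_β)²/d².
- Two-sided: 2(1.960 + 0.842)²/0.25 = 62.8, so 63 (64 with the exact t). Allowing for 20% loss gives 79 to 80 per arm by dividing by 0.8, or 76 to 77 by multiplying by 1.2.
- One-sided: 2(1.645 + 0.842)²/0.25 = 49.5, so 50 (51 with the exact t). Allowing for loss gives 63 to 64 by division, or 60 to 62 by multiplication.

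Only the one-sided normal formula multiplied by 1.2 returns 60 (50 × 1.2).

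**Step 2: unadjusted power with 48 per arm.** Noncentrality = 0.5 × √(48/2) = 2.449. Two-sided exact-t power is 67.9% (normal approximation 68.8%). One-sided power is 78% to 79%.

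**Step 3: adjusting for baseline.** Residual variance falls by the factor 1 − r², so interval width scales with √(1 − r²) and the effective d is 0.5/√(1 − r²). Two-sided, exact t:

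| r (assumed) | √(1 − r²) | Interval narrower by | Power |
|---|---|---|---|
| 0.2 | 0.980 | 2% | 69.6% |
| 0.3 | 0.954 | 5% | 71.9% |
| 0.4 | 0.917 | 8% | 75.3% |
| 0.5 | 0.866 | 13% | 79.9% |
| 0.6 | 0.800 | 20% | 85.8% |
| 0.7 | 0.714 | 29% | 92.4% |

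The gap to 80% is 80 − 67.9 = 12.1 points. At r = 0.2 adjustment closes 1.7/12.1 = 14% of it, and at r = 0.3 it closes 4.0/12.1 = 33%. Half is closed at r of about 0.37, and essentially all at about 0.5, where 48/(1 − 0.25) = 64 is the effective number per arm.

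**Step 4: adjusting for university alone.** Residual variance is multiplied by 1 − ICC. Power becomes 68.2%, 70.0% and 72.3% at ICC 0.01, 0.05 and 0.10. In the unadjusted test, the standard error is too wide by 1/√0.95 − 1 = 2.6% at ICC 0.05 and 1/√0.90 − 1 = 5.4% at ICC 0.10. True two-sided alpha is then about 4.4% and 3.9%, so the test is conservative and type I error is not inflated.

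**Step 5: cost in degrees of freedom.** Baseline takes 1 and university 9, leaving 96 − 12 = 84. At r = 0.5, power is 79.8% on 84 degrees of freedom against 79.9% with baseline alone (93).

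**The case against.** The strongest reply is that this is a condensed article. Model terms are commonly left to a fuller plan, and a GEE with unlisted terms is compatible with stratified randomisation. That stands for the GEE and the repeated-measures ANOVA. A reader might infer that every planned between-group analysis ignores baseline GIS and university, but the text does not support this: the GEE may contain both, and the ANOVA may include the baseline visit. The reply does not cover the t-test, which is named as a comparison and cannot carry either variable whatever a fuller plan says.

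A baseline visit entered as a time level is also not equivalent to a baseline covariate. If only baseline and 3 months were used, the group-by-time test would be a change-score test with variance factor 2(1 − r). Its power (normal approximation) is 54% at r = 0.3 and 69% at r = 0.5, against 73% and 81% with baseline as a covariate.

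Other replies also have force:

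- **Validity.** Under randomisation the unadjusted comparison is unbiased and, with balanced strata, slightly conservative. The issue is efficiency.
- **Power restored.** A reader might infer that adjustment recovers most of the missing power. That needs r above about 0.37, and the documents give no r. Baseline falls about two weeks after the death and the outcome months later, so a modest correlation is plausible.
- **Size of the shortfall.** It assumes a two-sided test. On the one-sided reading, power is already 78% to 79%.
- **Aim.** All power figures are for detecting a difference. The stated hypothesis is comparable efficacy with no margin, so power for that aim cannot be computed.
- **The 1-month data.** A linear model at 3 months alone would set aside scores that the planned GEE can use, which matters with 20% expected loss. The fix therefore allows either model.

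**Conclusion.** The point holds for the named t-test and its non-parametric substitute, and no further. Those tests leave out a baseline score the trial collects and the stratum by which it randomises, and a better method is available almost free.

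The narrowing of the interval, 2% to 29% for r from 0.2 to 0.7, depends only on the assumed r. The power gain, from about 68% to between 70% and 92%, also assumes 48 completers per arm, d = 0.5 and a two-sided 5% test for a difference. University adds little: about 0 to 4 points for an ICC of 0.01 to 0.10. The change is worth making, but the documents do not show that it would bring the trial to 80% power.

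**What to change.** State in the Planned analysis section that the primary comparison of 3-month GIS is a model with allocated arm, baseline GIS and university (10 levels). Either of two forms will do:

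- a linear model for the 3-month score; or
- the planned GEE on the 1-month and 3-month scores, with baseline GIS and university as covariates, arm-by-visit terms, and the 3-month contrast as primary.

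Report the adjusted mean difference with its 95% confidence interval. Do not use the unadjusted t-test as the deciding test. Use the same form for GHQ-28 and the two SF-12 component scores, each with its own baseline. CSQ-8 is first collected when the sessions end and so has no baseline; adjust it for university only.

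The cost is a sentence or two of text and about 10 degrees of freedom, which is negligible. No new data are needed, and the software already named can fit these models.
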